### Informed consent

#### Healthcare providers

Healthcare providers who provide care to patients in the targeted population will receive a study email from the coordinating center with an information sheet, along with a link to the online survey. The IRB has authorized waiver of consent documentation; thus, completion of the survey will imply consent. An item on the survey will ask the healthcare provider if they wish to participate in study interviews. Those indicating interest in interview participation will be contacted by the study Clinical Research Assistant (CRA) at the study coordinating center via email or telephone. Verbal consent will be obtained prior to interview initiation.

#### Childhood cancer survivors

There will be no interaction between the study team and cancer survivors. Study involvement includes abstraction of existing clinical information only.

### Approach

#### Effectiveness trial

The HPV PROTECT intervention will be implemented as standard of care (quality improvement), and will be evaluated across the six participating sites using a cluster-randomized stepped-wedge design. During the first year of the trial, all six participating sites will be assigned to the baseline (control) condition in which they will proceed with usual care and measure HPV vaccination rates of the targeted population (cancer survivors 9–17 years of age and ≥ 1 year following completion of therapy) using state vaccine registry data accessible via EMRs. In Year 2, three of the sites will implement *HPV PROTECT* while the remaining three sites will continue with usual care. In Year 3, the remaining three sites will implement *HPV PROTECT,* and sustainability of the intervention will be evaluated for the three sites that implemented *HPV PROTECT* in Year 2. In Year 4, sustainability (i.e., ongoing improvement in vaccine initiation rates) of the *HPV PROTECT* intervention will be evaluated across all six sites. Measurement of HPV vaccination rates using state vaccine registry data accessible via EMRs will continue across the entire 4-year period of the trial.

#### Implementation trial

To inform future dissemination of the intervention, we will use a mixed methods approach to estimate change in healthcare provider HPV vaccine-related knowledge and practice; evaluate healthcare provider perspectives regarding intervention feasibility, acceptability, and appropriateness in the pediatric oncology setting; and evaluate provider adherence (fidelity) to intervention components.

All of the targeted pediatric oncology healthcare providers at each clinic will be invited to complete electronically-administered surveys, yearly for four years, via *Research Electronic Data Capture (REDCap®)* [51], a secure password-protected, web-based research database, regarding their HPV vaccine-related knowledge, current HPV vaccine-related practices (e.g., provision of vaccine recommendations to parents/patients), their evaluation of the HPV PROTECT intervention components, and their sociodemographic information (e.g., age, sex, education, role, years of experience). Healthcare providers who complete surveys will be asked to indicate if they would like to participate in qualitative interviews in the survey year during which the participant’s site is implementing the HPV PROTECT intervention. Healthcare providers who indicate interest in interview participation will be invited to participate in telephone or secure web-based interviews regarding feasibility and acceptability of the intervention components and barriers/facilitators to implementation of the intervention. Interviews will be recorded and transcribed by the coordinating center CRA. Personal identifiers will be removed from the data by the CRA following data collection. Results will be reported in aggregate without personal identifiers.

### Randomization

In this stepped-wedge cluster-randomized design, randomization will occur at the site level, with three sites randomized to begin the intervention in Year 2, and three sites randomized to begin the intervention in Year 3 (Fig. 3). There is no difference in the intervention between the two groups other than the intervention start date. The study’s stepped-wedge design incorporates a control period for all participating sites during Year 1, allowing for collection of baseline vaccination rates, thus avoiding historical comparisons. Before the beginning of Year 2, sites will be randomized according to the stepped-wedge design. The sites assigned to the control condition in Year 2 (sites A, B, C) will be assigned to the intervention in Year 3, and the Year 2 intervention sites (sites D, E, F) will be moved to the post-intervention (sustainability) condition for Year 3. All sites will be assigned to the post-intervention (sustainability) condition for Year 4. The stepped wedge design will allow comparison of the primary outcome (HPV vaccine initiation rate; i.e., proportion of survivors in targeted population who have received ≥ 1 HPV vaccine dose, as of the last day of each study year) across groups (control vs. intervention), while allowing each site to serve as its own pre-intervention control, and using the control observations in Years 1 (all sites) and 2 (sites A, B, C) to estimate secular trends. Sustainability will be assessed in the post-implementation period, i.e., in Years 3 (sites D, E, F) and 4 (all sites) (Fig. 4).

**Fig. 3 Fig3:**
[figure not shown]
Stepped-wedge cluster-randomized trial design

**Fig. 4 Fig4:**
[figure not shown]
Study schema

### Measures

#### Healthcare provider data

Participating healthcare providers will complete the following:

*Healthcare Provider Electronic Survey*. The healthcare provider survey will be completed electronically via *REDCap®* yearly for 4 years in Years 1–4; estimated completion time is 15 min per year. The survey will ascertain the following data: Sociodemographics (age, sex, race/ethnicity, education); Clinical characteristics (provider license type [MD, NP, PA]; role [attending, staff, trainee], years of experience in current role, average number of survivors seen per week); provider HPV vaccine-related knowledge/practices (knowledge regarding HPV vaccine, familiarity with strategies to increase vaccine uptake, recall [or prior knowledge] of key messages in the training program, current practices related to the HPV vaccine (e.g., method used to assess survivor vaccination status, frequency and quality of recommendation for HPV vaccine, strategies used to promote HPV vaccination); and intervention evaluation (objective rating of feasibility, acceptability, appropriateness of the intervention in the pediatric oncology setting and provider fidelity to intervention components [e.g., vaccine recommendations, educational materials]).

*Healthcare Provider Qualitative Interview.* Semi-structured qualitative interviews will be conducted with those healthcare providers who opt-in to this portion of the study. The interviews will occur once, during the year that the healthcare provider’s site initiates the intervention; estimated interview duration is 30 min. Providers will be asked about their perceptions of the feasibility (perceived potential for success), acceptability (perceived need), and appropriateness (perceived fit) of the intervention to the pediatric oncology setting, and their adherence (fidelity) to intervention components (e.g., delivery of recommendations, developing and communicating vaccine action plans to parents and PCPs). Interviews will be conducted during the second half of Year 2 (sites D, E, F) and Year 3 (Sites A, B, C) via telephone or secure web-based platform by an interviewer from the coordinating center trained in qualitative interview techniques. An Interview Guide will be used and interviews will be recorded and transcribed verbatim.

#### Patient-level data

The intervention occurs at the clinic level, and medical record and vaccine registry data for the cancer survivor population will be accessed by the site CRA under a HIPAA waiver as part of each site’s QI initiative. The site CRA will abstract the following data elements from the medical record for each survivor added to the study roster: Diagnosis category (leukemia, lymphoma, solid tumor, central nervous system [CNS] tumor); age at diagnosis, time from diagnosis, and time off-therapy at cohort entry; history of hematopoietic cell transplant (yes/no; if yes: type, number, age); history of Chimeric Antigen Receptor (CAR)-T cell therapy (yes/no: If yes: number, age); sex; and race/ethnicity. The CRA will abstract the following additional visit-specific data elements from the survivor’s medical record for the initial clinic visit and for each subsequent clinic visit occurring during the study period: Age at visit, study year and week of visit, provider type (physician, advanced practice provider), study identification number of healthcare provider(s) providing care at clinic visit, visit type (in-person, telehealth), and insurance type.

Upon adding each survivor to the study roster, the CRA will access the state vaccine registry and abstract all HPV vaccine dose(s) and associated date(s) of administration occurring prior to the date of the survivor’s cohort entry visit. At least yearly throughout the data collection period (Years 1–4), the CRA will access the state vaccine registry and abstract any additional HPV vaccine dose(s) and associated date(s) of administration occurring since the most recent data abstraction. Additionally, dose(s) and date(s) of additional vaccines recommended for adolescents (i.e., meningococcal, Tdap, influenza and COVID-19), will be abstracted by the CRAs at the same timepoints, for use as co-variates in the analysis, as it is important to understand whether uptake of the HPV vaccine differs from uptake of the other recommended adolescent vaccines [52]. All data will be completely de-identified prior to submission to the study coordinating center; survivors with visits in more than one year will be linked so that multiple observations per survivor can be addressed in the analysis. Coded roster data (with no elements of personal health information [PHI]) will be submitted weekly by participating sites to the study coordinating center via the study’s REDCap® study database. Data quality will be monitored in real-time by the site CRAs for each individual site and by the CRA at the study coordinating center for the overall study, using the study Standardized Operating Procedures, which include detailed instructions for data collection, verification, and cleaning. Additionally, range checks for key variables, and warnings to prevent missing data, are built into the REDCap® study database.

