### Analytic plan

#### Effectiveness trial

Unless otherwise noted, all statistical tests will be two-sided. The main hypothesis of the intervention’s effect will be tested using a mixed effects logistic regression model including a random intercept for each site. The base model for HPV vaccine initiation for participant *i* at site* j* during year* y* without covariates will be:$$\mathrm{log}\left({Odds}_{initiation,i,j,y}\right)={\beta }_{0}+{\beta }_{1}\bullet {year}_{j,y}+{\beta }_{2}\bullet {x}_{intervention,j,y}+{b}_{j}$$

where $${year}_{i,j}$$ indicates the study-year of the visit, and $${x}_{intervention,j,y}$$ equals 0 if site *j* has not been exposed to the intervention by $${year}_{j,y}$$, and equals 1 if it has, and $${b}_{j}$$ is the random intercept for site *j*. The primary hypothesis will be tested by the significance of the coefficient $${\beta }_{2}$$ in the model, which will capture the initial year of active intervention. Exploratory aims include testing whether the intervention results in increased rates of series completion and whether there is a sustained intervention effect in increasing HPV vaccine initiation. The analysis for series completion will parallel the analysis for initiation, with the exception that the analytic cohort for each year will be limited to those who had not completed the series prior to their index clinic visit for that year. Sustained effects will be tested using a similar model augmented by specific coefficients for duration of time in the intervention arm:$$\mathrm{log}\left({Odds}_{initiation,i,j,y}\right)={\beta }_{0}+{\beta }_{1}\bullet {year}_{j,y}+{\beta }_{2}\bullet {x}_{intevention,j,y}+{\beta }_{3}\bullet {x}_{2int,j,y}+{\beta }_{4}\bullet {x}_{3int,j,y}+{b}_{j}$$

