In this model, $${\beta }_{1}$$ will continue to account for a constant secular trend, while $${\beta }_{3}$$ will allow for an additional effect in the 2^nd^ year of intervention and $${\beta }_{4}$$ will similarly allow for an additional incremental effect in the third year. Thus, the log odds of initiation for a participant at site *j* in year 4 for a site in the third year of intervention will be estimated as $${\beta }_{0}+{\beta }_{1}\bullet 4+{\beta }_{2}+{\beta }_{3}+{\beta }_{4}$$ + $${b}_{j}$$. While hypothesis testing will be included in the exploratory aims, the focus will be on reporting estimated rates of outcomes and intervention effects with confidence intervals. For each outcome, secondary analyses will include patient age at visit, sex, insurance type, and race/ethnicity as covariates to improve the precision of estimates and provide an estimated standardized prevalence. We will also evaluate the impact of clinic level factors on vaccination initiation rates (e.g., clinic volume, provider characteristics, practice size, geographic location, and baseline initiation rates) as fixed effects. We will also report the HPV vaccine initiation rate among survivors who were vaccine-naïve at cohort entry (i.e., incidence of vaccine initiation). Last, we will perform subgroup analyses stratified by relevant biological variables (i.e., age at visit, sex, and race/ethnicity groups). For survivors who complete > 1 clinic visit/study year, the number and timing of subsequent clinic visits during the study period will be included as covariates in secondary analyses. Patients who develop a relapse or subsequent malignancy requiring active cancer treatment at any time during the study period will be removed from the data set as of the date of diagnosis of the relapse or subsequent malignancy. Parallel analyses will further consider providers as random effects within sites, adding a random intercept for each provider. Given the potential complexity of correlation structures and nesting, the main hypothesis tests will also be reported using permutation testing. As an example, for permutation testing the main effect based on coefficient $${\beta }_{2}$$, for multiple (> 1000) iterations, participants will be randomly assigned to sites and the models fit to develop an empirical distribution for estimates of $${\beta }_{2}$$ under the null hypothesis of not different. The p-value of $${\beta }_{2}$$ (with genuine assignments) will be estimated from distribution of coefficients estimated from the permutations.

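### Later clinic visits, and other-vaccine doses not limited to the time before exposure, are planned as covariates and can bias the secondary adjusted estimates; the primary test is unaffected

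*Protocol article*

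**What the plan says.** **Other vaccines (Patient-level data).** Doses and dates of four other vaccines are collected alongside the HPV doses: "meningococcal, Tdap, influenza and COVID-19), will be abstracted by the CRAs at the same timepoints". The use given is "for use as co-variates in the analysis". The analysis is not named. The time points are two. At roster entry, doses "occurring prior to the date of the survivor’s cohort entry visit" are taken. After that, "At least yearly throughout the data collection period (Years 1–4), the CRA will access the state vaccine registry". The reason given is that "it is important to understand whether uptake of the HPV vaccine differs from uptake of the other recommended adolescent vaccines".

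**Later visits (Analytic plan, Effectiveness trial).** For survivors with more than one visit in a study year, "the number and timing of subsequent clinic visits during the study period will be included as covariates in secondary analyses".

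**Primary model (same section).** The base model is introduced with the words "without covariates will be" and holds only study year, intervention status and a random site intercept. "The primary hypothesis will be tested by the significance of the coefficient" of intervention status, beta2.

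**Listed secondary covariates (same section).** These are age, sex, insurance and race/ethnicity, included for precision. The other vaccines are not on the list.

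**Outcome (Randomization).** At least one HPV dose by the last day of the study year.

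**The concern.** Covariate adjustment for precision is safe only for variables that the intervention cannot change. The Provider toolkit section describes a Vaccine Action Plan that tells families where to get the HPV vaccine if the oncology clinic cannot give it, such as a pharmacy, a primary care office or a health department. Other adolescent vaccines may be given at the same encounter. A plan for vaccination may also change how often, or when, a survivor returns to clinic.

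If the intervention does change these variables, conditioning on them does two things. It removes the part of the effect that runs through vaccination encounters. It also opens a non-causal path through vaccine-seeking behaviour, which influences both HPV and other vaccination. At stake are the secondary adjusted estimates and the standardised prevalences built on them.

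**Working it through.** **Step 1. Which results are exposed.** The beta2 test comes from the base model, which has no covariates, so it cannot be affected. Visit adjustment is stated for secondary analyses only. The other vaccines are assigned to an unnamed analysis and are missing from the list of secondary covariates, so the two sections do not agree on whether they enter a model.

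**Step 2. Order in time.** Subsequent visits come after the year's index visit by definition. The wording covers the whole study period, so it can take in visits after the year-end at which the outcome was fixed. Other-vaccine doses abstracted yearly through Year 4 include doses given after a site has started the intervention. Doses before cohort entry are also recorded, with dates, so a pre-exposure version is available, but the text does not restrict itself to it.

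**Step 3. Use against purpose.** Whether HPV uptake differs from uptake of other vaccines is a comparison of outcomes. Entering the other vaccines as adjustment variables does not answer it.

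**Step 4. The plan's own figures.** The protocol plans for 48.2% against 57.0%, which is 57.0 - 48.2 = 8.8 points (it prints 8.7), or an odds ratio of (0.570/0.430)/(0.482/0.518) = 1.42. A plain two-proportion check with 636 per arm (half of 1273) and two-sided alpha 0.05 (assumed; the protocol states none) gives

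power = Phi[(0.088 - 1.96 x 0.0280)/0.0279] = Phi(1.19) = 88.2%,

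which is compatible with the stated figure of over 80%. It ignores site and period effects and does not reproduce the protocol's simulation. The point here does not depend on power; only the two rates are carried forward.

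**Step 5. Possible size of the distortion, other vaccines only.** A simulation of 400,000 survivors per setting, without site or year effects:

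- X = exposure (probability one half); U = vaccine-seeking trait, standard normal.
- Other-vaccine receipt V: logit P(V) = -0.5 + ln(OR_V) X + 0.8 U.
- HPV initiation Y: logit P(Y) = a + b X + ln(s) V + 0.8 U, with a and b solved so that the rates are 48.2% and 57.0%.
- Logistic regression of Y on X, with and without V; effects are given as standardised risk differences.

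OR_V, s, the intercept -0.5 and the weight 0.8 are all assumptions. The protocol gives none of them.

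| Assumed OR_V | Unadjusted, points (s = 1, 2, 4) | Adjusted for V, points (s = 1, 2, 4) |
|---|---|---|
| 1 | 8.6, 8.7, 8.8 | 8.6, 8.7, 8.8 |
| 1.2 | 8.7, 9.0, 8.7 | 8.2, 7.9, 7.2 |
| 1.5 | 8.5, 8.9, 8.7 | 7.5, 6.6, 5.2 |
| 2 | 8.8, 8.9, 8.7 | 7.0, 4.9, 2.6 |

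The first row shows no distortion when the intervention leaves other vaccines alone. The s = 1 column shows a loss even when V has no effect on HPV initiation (8.8 to 7.0 points at OR_V = 2). That loss comes through U alone. The risk difference is the safer scale: with OR_V = 1 the adjusted odds ratio moves from 1.43 to 1.52 at s = 4 with no bias in the risk difference.

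No size was computed for the visit covariates.

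**The case against.** The case on the other side is substantial, and much of it stands.

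- **A reader might infer that the trial's main result is biased.** It is not: the primary model has no covariates.
- **A reader might infer that adjustment could erase the whole effect.** An example can be built where it does, but only by assuming that the entire effect passes through other-vaccine receipt. No figure in the protocol supports that, and none of the settings above gives zero.
- **A reader might infer that the trial gives up its check on outside shocks.** It does not. Dated doses of the comparison vaccines are collected, the stated reason is a comparison, and nothing rules it out.
- **Neither route of bias is shown.** The protocol does not say that the intervention changes other vaccines or visit frequency. Its Background describes return visits as surveillance and survivorship care.
- **The other vaccines cannot serve as strict negative controls.** If the intervention may change them, they are not a clean null. This limits the remedy and is reflected in the fix.
- **A condensed article leaves model detail to fuller documents.** True, and the lack of a full model is not the complaint. The complaint is about two uses that are stated: vaccines as covariates with no limit on dose date, and subsequent visits as covariates.

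The planned sensitivity analysis for visits late in the year (Discussion) addresses unequal follow-up. It does not remove subsequent visits from the secondary models.

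**Conclusion.** The point holds for the secondary adjusted estimates only, and as a possibility rather than a demonstrated bias. Subsequent visits follow exposure and may postdate the outcome, and this needs no assumption. Whether adjusting for them, or for post-exposure vaccine doses, distorts the estimate depends on how far the intervention changes them. For other vaccines, under the assumptions listed, the range runs from no distortion of an effect of about 8.7 points down to an adjusted estimate of 2.6 points, the latter at an odds ratio of 2 on receipt with a strong link (odds ratio 4) between receipt and HPV initiation. It is worth correcting because the bias is avoidable and the stated use does not serve the stated purpose.

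**What to change.** 1. **Patient-level data.** Allow as covariates only other-vaccine doses dated before the year's index visit. In years after a site's first intervention year, survivors already seen under the intervention need an earlier cut-off: their first visit under it. Add the restricted vaccine variables to the list of secondary covariates, or state that they are not used.
2. **Comparison outcomes.** Fit the same model to later uptake of meningococcal, Tdap, influenza and COVID-19 vaccines and report it beside the HPV result. Call these comparison outcomes, not negative controls, because spillover is possible.
3. **Analytic plan.** Drop the number and timing of subsequent visits from the effect models, or label models that contain them descriptive. Use index-visit week, which is already collected, to handle unequal time to year-end.

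The cost is a change of wording and a few extra model fits on data already collected. The primary analysis does not change.

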### Outcomes

#### Primary outcome

Change in survivor HPV vaccine initiation rates one year following intervention implementation, measured using state vaccine registry data accessed via the EMR at each participating site as part of the QI project associated with this research. The primary outcome will be measured as of the final day of the intervention year (Year 2 for sites DEF, Year 3 for sites ABC).

